#### Cost-effectiveness measures

##### General quality of life

The EuroQol five dimensions, five levels generic health index (EQ-5D-5 L [69]) is a standardized self-report questionnaire consisting of five dimensions (mobility, self-care, usual activities, pain/discomfort, and anxiety/depression). Participants rate each dimension on five levels (ranging from ”no problems” to ”extreme problems”). Consequently, 243 distinct health states are defined, each with a unique utility score, ranging from 1 (perfect health) to 0 (death). The health descriptions will be linked to empirical valuations of the Dutch general public, allowing utilities to be computed [70].

While the EQ-5D-5 L is the gold standard for computing utilities and economic evaluations, it is limited in the sense that it mainly addresses physical aspects of the health experience and might not be appropriate for assessing mental health problems. For example, psychiatric patients may not endure many physical problems while still experiencing considerable distress. Approaching outcomes for individuals by focusing on people’s capabilities, instead of physical aspects of health, might therefore be more suitable for individuals with psychiatric conditions [71]. The ICEpop CAPability measure for Adults (ICECAP-A [72]) shows promise in going beyond the general health status and capturing broader outcomes for individuals. The questionnaire aims to measure five capabilities on a 4-point scale, namely stability (the extent to which someone feels consistency and safety in life), attachment (the extent to which someone feels love, friendship, and support in life), autonomy (the extent to which someone can be independent in life), achievement (the extent to which someone can make progress in life), and enjoyment (the extent to which someone can enjoy life). The five items attempt to capture an individual’s capability to live a life that he/she values. The ICECAP-A has been found to be a valid measure of one’s capabilities [73] and appears to be suitable for economic evaluation of outcomes of adults with mental health problems, such as depression [71].

##### Direct medical costs

The Trimbos/iMTA questionnaire for Costs associated with Psychiatric Illness (TiC-P, Midi version [74]) will be used to calculate the total direct medical costs. The TiC-P assesses medical treatment utilization (e.g., number of contacts with the general practitioner, medical specialists, and paramedics) and medication use during the last 3 months. Additionally, the Midi version of the questionnaire is significantly shorter, reducing the burden for participants, while retaining 90% of the total cost estimated by the full version [74]. The direct medical costs will be calculated using the Dutch guidelines for cost calculations in healthcare [75]. Reference unit prices of the corresponding health care services will be applied [75, 76].

#### Demographics, closeness, self-esteem, and attrition

##### Demographic

A self-designed questionnaire will be used to gather demographic information. More specifically, gender, age, educational level, country of origin, and work situation will be assessed. Three additional questions are included, to inform about Internet access, the severity of eating problems, and whether participants have previously been or are currently in treatment for an ED.

##### Inclusion of Other in the Self scale

The Inclusion of Other in the Self scale (IOS scale [77]) will be sent to participants allocated to one of the conditions with support by an expert patient at week 3 of the intervention to assess perceived similarity and feelings of closeness early in the working relationship between expert patient and participant. The IOS scale is a one-item instrument in which seven images with two circles representing the self and the other that overlap increasingly, from zero overlap to almost complete overlap, are presented to participants. The participants can then rate their relationship with another person by choosing the best fitting image. More overlap between the circles indicates a closer bond. This scale is particularly suited for the current study, since it can be used for any type of relationship, and not only romantic partners, friends, and acquaintances [78]. Furthermore, Gächter, Starmer, and Tufano [79] conducted three studies to examine the validity and reliability of the IOS scale. A very strong convergent validity with a closeness index derived from six other relationship inventories (Spearman correlation of 0.85) was found. The authors conclude that the one-item IOS scale is easy to use, highly reliable, and a very powerful measure of closeness of relationships.

##### Rosenberg Self-Esteem Scale

The Rosenberg Self-Esteem Scale (RSES [80]) is the most used measure of global self-esteem. It consists of 10 items measuring the affective evaluation of the self. The items are presented on a 4-point scale ranging from ”totally agree” to ”totally disagree”. The questionnaire has been found to have satisfactory psychometric properties [81]. The Dutch translation of the RSES originates from Franck, De Raedt, Barbez, and Rosseel [82], who created the translation using forward and back translation methods. Two studies indicate high internal consistency and good convergent and divergent validity of the Dutch version of the RSES [82, 83].

##### Attrition follow-up

Attrition can refer to participants no longer using the intervention (non-usage attrition) or to participants completely dropping out of the study (dropout attrition). Two questions were designed to investigate why people dropped out of the study or no longer used the intervention to which they were allocated.

If a participant fails to complete a monitoring assessment, an e-mail with a reminder will be sent. A week later, participants receive another reminder. This reminder includes a question asking whether one wishes to continue Featback or not, and, if not, participants are asked to answer one more question by writing down their reason(s) to quit the intervention (i.e., attrition follow-up question).

If a participant fails to complete a T1, T2, T3, T4, or T5 assessment within 1 week, an e-mail with a reminder will be sent. A week later, a second reminder will be sent. This reminder includes a question asking whether one wishes to further participate in our study, and, if not, participants are asked to answer one more question by writing down their reason(s) to quit the study.

### Participant procedures

Figure 1 depicts an overview of the procedures that participants will undergo throughout the study. After recruitment, interested individuals can send an e-mail to the main researcher. Consequently, they will be sent a reply in which they are thanked for their interest and invited to complete a screening questionnaire. Participants who complete the screening questionnaire receive an e-mail including feedback on their results and a notification about whether or not they are considered eligible for the study.

Participants who are eligible for the study will be sent an e-mail which contains an explanation of the study and corresponding procedures. Participants then have to give their informed consent to continue with the study. Agreeing to the terms of participation will be possible through clicking several checkboxes. Because informed consent is given online, the system will generate a pop-up at the end of the form with a question asking participants are sure they give consent to participate in the study. Here, participants will also be notified that they can leave the study at any time for any reason if they wish to do so, without any consequences. Subsequently, participants are presented with a link to the first assessment (T0). After giving informed consent and filling in the baseline measurement, participants will be randomized to one of the four conditions and will receive an e-mail about the condition to which they are allocated and the corresponding procedures.

At this point, the 8-week period of intervention (or waiting) starts. At post-intervention (T1, week 8) and for all follow-up measurements (T2, 3 months; T3, 6 months; T4, 9 months; T5, 12 months) participants will be asked to complete the corresponding questionnaires. Finally, participants will receive an e-mail in which they are thanked for participating in the study. Participants who take part in the study receive 10 euros as compensation in the form of a gift voucher after the last measurement. Additionally, participating in the study will be made more personal and rewarding in the form of an e-mail sent to participants after every T1–T5 assessment, in which gratitude for participation is expressed. Hopefully, these incentives increase intervention usage and reduce attrition in the study.

### Ethical considerations

Participants will be asked to complete questionnaires at baseline, a weekly monitoring questionnaire during the intervention, and a three-monthly questionnaire during the follow-up phase. This has been found to be an acceptable burden by a client panel. Earlier research with a comparable design showed no adverse effects of Featback [20], and participants in all conditions, including the waiting list, are allowed to seek treatment outside the study.

Individuals who enter the study and report severe ED symptoms during the screening or who develop severe ED symptoms during the intervention will be sent an e-mail stating that their scores indicate serious ED problems and that professional help is warranted. More specifically, if a participant indicates a BMI of 15 or lower or reports compensatory behavior or bingeing at least every day during a week in the screening or Featback monitoring assessment, an alarm signal will be sent to the main researcher. If the participant is allocated to the Featback only or waiting list control condition, the participant will be sent an e-mail in which the researchers’ concerns about the severe ED symptoms are expressed and recommendations for professional help are included. If the participant is allocated to one of the expert-patient support conditions and the participant has not scheduled an appointment for this week, an e-mail will be sent to encourage the participant to schedule an appointment. During the support session, the expert patient will discuss the alarm signal and severe ED symptoms and stimulate the participant to seek professional help. Similarly, participants in the support only condition who indicate (increasingly) severe problems in their chats or mails will be encouraged to seek professional help in subsequent sessions. If participants with severe ED symptoms do not make an appointment for a support session, the e-mail as described for participants in the Featback only or waiting list control condition will be sent.

Nevertheless, individuals with severe ED symptoms will not be excluded from the study, as there is no reason to withhold Featback or expert-patient support. It could well be that these individuals are reluctant to seek (face-to-face) treatment or that they are not fully aware of the severity of their symptoms. Accordingly, Featback may serve as an important first step to regular healthcare, because it could help individuals with the process of recognition and acknowledgement of the severity of their ED symptoms and the need to seek professional help (see also [18]). Moreover, Featback and/or the individualized support from expert patients may serve as an important and unique source of support that could help individuals deal with their (eating) problems more effectively.

Expert patients are instructed to refer participants who report suicidal ideation to the website of ”Stichting 113” [84]. The goal of this organization is to prevent suicide. They have psychologists, psychiatrists, and trained volunteers in employment who are accessible 24 h a day via telephone and chat.

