#### Waiting list control

Participants will be placed on a waiting list for 14 months (matching the participation duration of participants in the other conditions; 8-week intervention period plus 1 year follow-up), after which they will be offered 8 weeks of Featback with support from an expert patient. Participants in this condition will be asked to complete the same assessements as participants in the other conditions (i.e., T0-T5). Note that participants in all conditions are allowed to seek and receive treatment and take medication.

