##### Intervention usage

Intervention usage will be operationalized by the amount of weekly monitoring assessments a participant has completed during the intervention period (range 0–8). Additionally, to be able to further investigate the relation between intervention usage and the effectiveness of Featback, the number of received support sessions of participants (one for each received e-mail or chat session) will be recorded.

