### Statistical analyses

All statistical analyses will be conducted in SPSS version 25 and the R statistical programming environment [85]. A two-tailed significance level of *α* = .05 will be maintained throughout the analyses unless indicated otherwise. All analyses will be conducted according to the intention-to-treat (ITT) approach. This means that all participants who underwent randomization, even those who withdrew from the study or deviated from the protocol, are included in the analyses. For the effectiveness analyses, both ITT and completers analyses will be conducted. A participant is considered a completer when he/she has completed at least five monitoring assessments (i.e., Featback only condition), five support sessions (i.e., expert-patient support only condition), or both (i.e., Featback plus expert-patient support condition).

Missing data will be handled using multiple imputation [86]. Multiple imputations using predictive mean matching will be conducted in the statistical programming environment R [85]. Interactions will be taken into account in the imputation procedure [87]. Multiple imputation methods have several advantages over complete-case analyses or single imputation techniques and are therefore highly recommended [86, 88].

Homogeneity of groups (i.e., between-group differences) will be assessed at baseline (T0) using chi-square tests for categorical variables and ANOVAs for continuous variables. Additionally, homogeneity of variances will be assessed using Levene’s statistic, and non-parametric testing will be used when appropriate.

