#### Intervention effectiveness analyses

To investigate the effectiveness of Featback with and without weekly expert-patient support, within-group and between-group effect sizes (Cohen’s *d*) will be calculated (i.e., the effects of time and intervention) using the pooled standard deviation of each group. We are mainly interested in the effect from baseline to post-intervention (T0–T1), but to see if effects are maintained over the short and long term, analyses will be repeated for T1–T3 and T1–T5 respectively.
 To answer the first and main hypothesis that the active interventions (i.e., Featback, expert-patient support, and Featback plus expert-patient support) are more effective than a waiting list in reducing ED symptomatology (i.e., primary outcome EDE-Q global score), the three active intervention conditions will be compared to the waiting list condition. Repeated measures ANOVA will be used for T0–T1 to test this hypothesis. To see if the effects are maintained, these analyses are repeated for T1–T3 and T1–T5. The second hypothesis was that the combination of Featback and expert-patient support would be more effective than Featback or expert-patient support alone. A repeated measures ANOVA with post hoc tests will be conducted to compare T0–T1 differences in ED symptomatology between the four conditions. The post hoc analyses apply the Bonferroni correction for multiple testing. To see if these effects are maintained, these analyses are repeated for T1–T3 and T1–T5.

These confirmatory analyses will be repeated controlling for significant baseline variables (i.e., age, duration of ED psychopathology, number of psychological healthcare appointments). Additionally, the main analyses will be repeated for completers only.

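### The only questionnaire alarm for severe symptoms after randomisation is Featback monitoring: two arms lack it for 8 weeks, all four lack it after T1, and severe EDE-Q answers trigger no stated response

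*Protocol article*

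**What the plan says.** All references are to the protocol article.

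- **Commitment.** Ethical considerations says that people with severe symptoms at screening, and people who develop them during the intervention, will be told by e-mail that professional help is warranted.
- **Trigger.** The same paragraph then specifies the rule: a BMI of 15 or lower, or daily bingeing or compensatory behaviour, "at least every day during a week in the screening or Featback monitoring assessment, an alarm signal will be sent to the main researcher". No other source is named.
- **Response by arm.** Featback-only and waiting-list participants get the advice e-mail. In the support arms the expert patient discusses the alarm. There is a fallback: "If participants with severe ED symptoms do not make an appointment for a support session, the e-mail as described for participants" in the other two arms is sent. Support only has one extra route: "participants in the support only condition who indicate (increasingly) severe problems in their chats or mails will be encouraged" to seek professional help.
- **Where monitoring runs.** The weekly questionnaire is described under Interventions, Featback. Intervention usage counts "the amount of weekly monitoring assessments a participant has completed during the intervention period", range 0–8. Completers are defined by "five monitoring assessments (i.e., Featback only condition), five support sessions (i.e., expert-patient support only condition", or by both in the combined arm.
- **What every arm completes.** Waiting-list participants "will be asked to complete the same assessements as participants in the other conditions". The EDE-Q has 6 behaviour-frequency items with 28-day recall (Primary outcome measures). After the T0–T1 comparison, "analyses will be repeated for T1–T3 and T1–T5 respectively".

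**The concern.** The commitment is worded for people in the study generally, but the trigger rule can act on a questionnaire after randomisation in only two of the four arms, and only for 8 weeks. Ethical considerations names the waiting list as a recipient of the advice e-mail, yet only a screening result can set that e-mail off there. Support only depends on the participant booking a session and disclosing.

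Severe illness is not an exclusion. The article itself says that such people may not fully realise how severe their symptoms are, so freedom to seek outside care does not replace being told. As written, a participant in any arm could report daily purging at T1 or later and the stated rule would prompt nothing. What is at stake is participant safety at small cost. The validity of the primary analysis is not in question.

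**Working it through.** The plan states no figure to reproduce. The check sets the sections side by side and then counts.

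**1. Inputs**
- 88 per arm, 352 in total; 25% dropout T0–T1 (Sample size calculation).
- 8-week intervention, then 12 months (about 52 weeks) to T5 (Design).
- Alarm sources: screening and Featback monitoring (Ethical considerations).
- EDE-Q recall 28 days (Primary outcome measures). EDE-Q time points of at least T0, T1, T3 and T5 are inferred from Intervention effectiveness analyses, because Table 2 is not shown.

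**2. Who has an alarm source after randomisation**

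| Arm | 8 weeks to T1 | 12 months after T1 |
|---|---|---|
| Featback | weekly monitoring | none stated |
| Featback + support | weekly monitoring | none stated |
| Support only | chat or e-mail content | none stated |
| Waiting list | none | none stated |

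- Arms without a questionnaire alarm in the 8 weeks: 2 × 88 = 176 of 352 (50%), of whom 88 (25%) have no source at all.
- Total span 8 + 52 = 60 weeks. The between-arm difference occupies 8/60 = 13% of it. The other 52/60 = 87% is alike in all arms.
- Questionnaire alarm coverage is at most (176 × 8)/(352 × 60) = 1,408/21,120 = 6.7% of planned person-weeks. This assumes that every weekly questionnaire is completed.

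**3. What an EDE-Q flag can see**
- At T1: 28/56 days = 50% of the intervention period, and only after the fact.
- After T1 (364 days): 2 × 28/364 = 15% if T3 and T5 carry the EDE-Q; 4 × 28/364 = 31% if T2 to T5 all do.

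**4. Threshold on the 28-day count**
- Entry criterion of one episode a week: 1 × 4 = 4.
- One week of daily behaviour: at least 7.
- Daily behaviour throughout: at least 28.

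A cut near 7 lies close to the entry level and would flag many participants. A cut near 28 flags fewer but misses a single daily week.

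**5. Volume at T1 (assumption)**

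Expected T1 responders: 88 × 0.75 = 66 per arm, 352 × 0.75 = 264 in total. The share above a high cut is not in the document. If it were 2% to 10%:
- per arm, 66 × 0.02 = 1.3 to 66 × 0.10 = 6.6 e-mails;
- in total, 264 × 0.02 = 5.3 to 264 × 0.10 = 26.4.

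Flags can recur. At 10% on each of T1, T3 and T5, with full response, the share ever flagged runs from 10% (same people each time) to 1 − 0.9³ = 27% (independent). These rates would not apply to a cut near 7.

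**The case against.** **What stands.**
- The flag acts at week 8, so it leaves the between-arm gap inside the 8 weeks open. Extending weekly monitoring to the other arms would close it, but monitoring is part of the Featback intervention being tested.
- Existing protection is real: a screening alarm and screening feedback in all arms, outside treatment allowed, the chat or e-mail route, and the fallback e-mail. None of these, however, is a questionnaire alarm after randomisation for the waiting list or support only.
- Alarm handling is not free. Alarms go to the main researcher, and Cost-effectiveness analyses charges a psychologist's response to severe cases to Featback. The fix therefore needs a costing rule.
- The e-mail urges people to seek care, so help-seeking and healthcare costs are the outcomes most exposed. The document gives no basis for sizing that effect.

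**Stronger readings that the document does not support.**
- *A reader might infer that the protocol breaks its promise during follow-up.* The commitment covers screening and the intervention only. The 12 months after T1 are a design weakness.
- *A reader might infer that the waiting list alone is unprotected for 14 months.* After T1 no arm has a stated source.
- *A reader might infer a bias in the T0–T1 comparison.* Nothing in the text shows one.
- *A reader might instead infer that all arms are monitored*, because Ethical considerations lists "a weekly monitoring questionnaire during the intervention, and a three-monthly questionnaire during the follow-up phase" without naming arms. The Featback section, the completer definition and the separate support-only sentence all point to the Featback arms.

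**Condensed article.** The full protocol may say more about follow-up answers. The point rests on a trigger rule that the article states explicitly, not only on silence.

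**Conclusion.** The point holds as a cheap safety improvement. For 8 weeks, 88 planned participants have no alarm source and another 88 have only session content. After T1 all 352 have no stated source, although the trial collects answers that could supply one. This is not an error in the sample size or in the primary analysis.

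The conclusion assumes that monitoring is confined to the Featback arms, which three sections support, and that the EDE-Q is given at least at T1, T3 and T5. Its use at T2 and T4 is unconfirmed. The number of participants who would be flagged, and the effect of the e-mail on follow-up outcomes, are unknown. The 2% to 10% range is illustrative.

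**What to change.** 1. In all four arms, apply one automated flag to the EDE-Q binge and compensatory-behaviour frequency items at T1 and at each later assessment that carries the EDE-Q (at least T3 and T5). Send the existing advice e-mail automatically.
2. Fix one threshold in advance at the high end, about 28 occurrences in 28 days, and accept that a single daily week is missed.
3. Log alarms by arm and time point, and report the counts beside the help-seeking and cost results.
4. Treat the cost of the automated e-mail identically in every arm, so that it does not distort the comparison with usual care.
5. Minor clarification: the four monitoring items, as described, include no weight, so state whether the BMI criterion operates at screening only.

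**Cost.** Some protocol text, a rule on answers already collected, and a costing line. E-mails already go out after each of T1–T5, so the channel exists. Recruitment has started, so ethics review may be needed.

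**Downside.** Some extra prompts to seek care, under the same rule in every arm. These could modestly affect follow-up help-seeking, healthcare costs and the T1–T3 and T1–T5 EDE-Q results. The primary T0–T1 comparison is untouched, because the first flag follows the T1 answers.
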